EYEP has a dual focus: addressing the consequences of abuse and neglect on children’s brain development, and redressing their learning deficiencies. Jack Shonkoff has argued that most current programs for children from disadvantaged backgrounds do not have this dual focus – instead they mainly provide enriched learning experiences for children and parenting education for mothers. He suggests that a better approach for redressing inequalities in skill development is to adopt the dual focus: ‘by linking high-quality pedagogy to interventions that prevent, reduce, or mitigate the disruptive effects of toxic stress on the developing brain’
[30], p.982]. It is exactly this task that EYEP is taking up.

EYEP employs a holistic model in early education and care. Key features are high staff/child ratios (1:3 for children under 3 years, and 1:6 for children over 3 years), qualified staff, a rigorously developed curriculum, and the use of relationship-based pedagogy. The program involves direct intervention with a child to address his or her identified needs, reverse developmental delays, and reduce the impact of risk factors and adverse events. An innovative feature of the program is a trans-disciplinary model which includes an education leader who has graduate qualifications in early childhood curriculum (supported by a part-time early childhood curriculum consultant), an in-house infant mental health consultant, and family support consultant. There is a focus on developing relational pedagogical strategies to reduce the behavioural and emotional dysregulation resulting from living in a situation of toxic stress to enable the children to be more available for learning.

The basis for **care** in EYEP is an attachment-focused, trauma informed, primary-care model which recognises the significance of respectful, responsive relationships for every child’s learning and development. Every child is allocated a key worker who is that child’s primary carer. Purposeful, warm greetings and a clear idea of the routines and opportunities of the day are essential components of the model, which help to give children a sense of security, predictability and consistency. The objective of the primary care model is to encourage the fostering of significant attachments for children who are likely to be experiencing disrupted and compromised attachment relationships in their home environments.

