### Data analysis

The data analysis will identify the impact of ‘Intention to treat’ at the level of the individual child. The analysis will compare the change in an outcome measure (at time of data collection minus at baseline) for children in the intervention group with children in the control group. Impact evaluations will be conducted on outcomes measures after the 12, 24 and 36 month data collections as well following the data collection after the commencement of the first year of schooling.

For comparisons between the randomised intervention and control groups from the trial it should be possible to estimate the program impact as the difference in mean outcomes between those groups. For continuous outcome variables this will be the difference in mean changes in the outcome between intervention and control groups. For categorical outcome variables it will be differences in the change in the proportions of children in each category between intervention and control groups. For comparisons between the EYEP intervention group and the control group from LSAC a quasi-experimental matching method (difference-in-difference) will be used. Statistical significance will be established via t-tests for individual outcomes or Hotelling T tests for groups of outcomes.

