### Sample size and power calculations

The sample size has been determined taking into account both the numbers of observations needed to have sufficient power to detect likely effect sizes and the capacity of the CPS childcare centre where EYEP is being implemented. There is no previous Australian study of an intervention similar to EYEP, therefore calculation of the required sample size has been done using impact sizes estimated for the Abecedarian project. Impact sizes from the Abecedarian project are above those for most other early years programs
[21], however, this can be attributed to its being an extensive and long-term intervention. The similar scale of intervention in EYEP makes Abecedarian an appropriate benchmark for this study. We use impact estimates from the Abecedarian project for IQ at 18 months and at 48 months (
[35] page 1918).

The sampsi routine in STATA was used to calculate the necessary sample size. When type one error is set at 0.05 and type two error set at 0.1 (power = 0.9), the minimum required sample size (per group) is 12 children based on the impact on IQ at 18 months IQ and 19 children based on the impact on IQ at 48 months. We then adjust this required sample size in two ways. First, we take into account that our sample will include families with multiple children. Based on the sample from the pilot phase of EYEP we estimate the number of children per family to be 1.35. We assume perfect correlation of outcomes between siblings which therefore requires expanding the minimum sample size by 1.35. Second, we incorporate an estimated attrition rate of 20 per cent per annum for the intervention and control groups (including item non-response). These adjustments result in a minimum sample size per group of 32 children. Hence it is expected that the sample size of 45 children in intervention and control groups will comfortably meet sample size requirements. It also provides a margin of safety in case standard errors in estimates of the impact of EYEP are larger than for the Abecedarian trial. All children in the Abecedarian trial were enrolled prior to reaching 6 months of age, while children recruited into the EYEP trial have been from a broader range of ages, up to 3 years. To the extent that age of enrolment is a source of variability in impact sizes, our estimates of impact size may therefore have larger standard errors than the Abecedarian study.

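### The planned child-level t-tests assume independent children, although EYEP children are cared for through key workers in one centre and siblings are allocated together

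*Protocol article*

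**What the plan says.** The Data analysis section sets an intention-to-treat comparison "at the level of the individual child" and then names the tests: "Statistical significance will be established via t-tests for individual outcomes or Hotelling T tests for groups of outcomes". It mentions no clustering of any kind.

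The programme description (Background, Approaches to dealing with the problem) makes the provider part of the treatment: "Every child is allocated a key worker", who acts as the primary carer. Staffing is given as "1:3 for children under 3 years, and 1:6 for children over 3 years". The sample-size section shows that EYEP runs at one site, since it cites "the capacity of the CPS childcare centre where EYEP is being implemented" as a constraint.

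Under Intervention and control group, control children receive parental or guardian care or attend other local centres and kindergartens, as their parents choose. Under Randomisation, all participating children of a family go to the same arm, including siblings born during recruitment.

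The sample-size section recognises one source of dependence: "First, we take into account that our sample will include families with multiple children". It assumes perfect sibling correlation and multiplies by 1.35. Key workers are not mentioned there.

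**The concern.** Children looked after by the same educator may develop more alike than children looked after by different educators, particularly in a programme built on an attachment to one carer. If one educator also completes the childcare educator questionnaires for several children, shared rating could add to the resemblance on those measures. Clustering by EYEP key worker can arise in the EYEP arm only, which makes the design partially nested. Family clustering arises in both arms.

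An ordinary t-test or Hotelling test ignores both. With positive correlation within workers, the variance of the EYEP mean is understated, intervals are too narrow and the 5% level is exceeded. A difference partly due to a few individual educators could also be read as the effect of the EYEP model. The authors accept that related children carry less information when they size the trial, but the analysis text does not carry this through, and the sizing does not extend it to providers.

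**Working it through.** **Inputs from the article.** 45 children per arm; type I error 0.05 (sidedness not stated, two-sided assumed); power 0.90; 19 per group before adjustment (IQ at 48 months, the larger of the two figures); sibling factor 1.35; attrition 20%; adjusted minimum 32 per group.

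**Inputs assumed.** Children per key worker, m = 3 or 6, taken from the staff ratios as a stand-in for caseload. Key-worker ICC 0.01 to 0.20, because the article gives none. Equal total variance in both arms, and no provider clustering among controls.

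**The article's own figure.** 19 × 1.35 / (1 − 0.20) = 32.06, which reproduces the stated 32.

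**Key-worker clustering in the EYEP arm only.**

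- Design effect in the EYEP arm: DE = 1 + (m − 1) × ICC.
- True SE of the difference divided by the t-test SE: r = √((DE + 1)/2).
- Actual two-sided level: 2 × (1 − Φ(1.96/r)).

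Example, m = 6 and ICC 0.10: DE = 1 + 5 × 0.10 = 1.5; r = √(2.5/2) = 1.118; 1.96/1.118 = 1.753; level = 0.080.

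The last column multiplies the article's 32.06 by (DE + 1)/2. This is a rough guide, since it treats the sibling and worker factors as multiplicative.

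| m | ICC | DE | r | Actual level | Minimum per group |
|---|---|---|---|---|---|
| 3 | 0.01 | 1.02 | 1.005 | 5.1% | 32.4 |
| 3 | 0.05 | 1.10 | 1.025 | 5.6% | 33.7 |
| 3 | 0.10 | 1.20 | 1.049 | 6.2% | 35.3 |
| 3 | 0.20 | 1.40 | 1.095 | 7.4% | 38.5 |
| 6 | 0.01 | 1.05 | 1.012 | 5.3% | 32.9 |
| 6 | 0.05 | 1.25 | 1.061 | 6.5% | 36.1 |
| 6 | 0.10 | 1.50 | 1.118 | 8.0% | 40.1 |
| 6 | 0.20 | 2.00 | 1.225 | 11.0% | 48.1 |

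**Check by simulation.** Ordinary t-tests, 45 v 45, 40,000 runs per setting. At ICC 0 the level was 4.9%. At ICC 0.05, 0.10 and 0.20 it was 5.6%, 6.0% and 7.6% (m = 3), and 6.6%, 7.7% and 10.8% (m = 6). This agrees with the formula.

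**Effect of losses.** Suppose 20% a year is lost at random over three years within fixed groups, so that 0.8³ = 0.512 remain. The expected number of retained group-mates falls to 2 × 0.512 = 1.02 (m = 3) or 5 × 0.512 = 2.56 (m = 6). At ICC 0.10, DE is then 1.10 or 1.26, and the level about 5.6% or 6.5%.

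**Sibling clustering.** Taking the article's 1.35 as a design effect in both arms, r = √1.35 = 1.162 and the level is about 9.2%, before any key-worker effect.

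**The case against.** The strongest points on the other side are these.

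- **The target of inference.** If the question is the effect of EYEP as delivered by these staff at this centre, worker effects are fixed and the t-test SE need not be too small. A reader might infer that the standard errors are too small whenever children of one worker resemble each other. The documents do not support that without a condition, because the target is not stated. The condition is plausible, however: the end of the section on approaches to the problem and the Discussion both present EYEP as informing wider services and national policy.
- **Caseload.** The article gives staff ratios and no key-worker caseload, and 1:6 applies only above age 3. Recruitment runs from 2011 to 2015 and participation to 2018, so workers and groupings may change. Sharing is an inference, though a near-certain one at these ratios. Rooms or fixed groups are not described, so no claim can rest on them.
- **Controls.** A reader might infer that controls share no providers. That is too strong: they come from one catchment and may attend the same local centre. What can be said is that they share no EYEP key worker.
- **Spill-over.** The Background remark on negative spill-over might be read as evidence of peer effects among EYEP children. It concerns effects on children without a background of neglect and abuse, so it gives no support here.
- **Size.** The ICC is assumed, losses shrink the clusters, and at ICC 0.01 the effect is trivial. This stands. The better documented dependence is between siblings, and a key-worker term alone would leave it unaddressed.
- **Condensed text.** Random effects and degrees of freedom are often left to an analysis plan, which is not shown and may deal with them. But the article does not leave the test open: it names tests that assume independence.

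**Conclusion.** The point holds conditionally. The article commits to tests that assume independent children, in a design where siblings are allocated together and EYEP children very probably share key workers. Provided that inference extends beyond these educators and that correlation within workers is positive, the EYEP-arm standard error is too small by a factor within the overall comparison of about 1.01 to 1.10 (three per worker) or 1.01 to 1.22 (six per worker) for an ICC of 0.01 to 0.20. The true level is then about 5.1% to 7.4%, or 5.3% to 11%.

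The upper end needs both an ICC of 0.20 and six children per worker throughout. Only in that setting does the rough minimum (48.1) pass the planned 45 per group, on the article's chain, which applies the attrition factor once. In the other settings the margin above 32 shrinks but remains. The sibling dependence that the article itself assumes gives about 9.2% if it too is ignored in the tests. This should be corrected, but it does not undermine the trial.

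**What to change.** 1. Keep a dated record of each EYEP child's key worker or workers while the programme runs, since it is harder to reconstruct later.
2. Replace the plain t-test with a model that has a family effect in both arms and a key-worker effect in the EYEP arm only, with small-sample degrees of freedom (Satterthwaite or Kenward-Roger). Handle groups of outcomes and categorical outcomes consistently with this.
3. Analyse all randomised children. State in advance how children who change worker, or who never attend and so have none, enter the model, because worker assignment is known only after randomisation.
4. State whether inference is to these educators or to the EYEP model more widely.
5. Report the estimated key-worker ICC with its interval.
6. Say in the sample-size section that the calculation allows for siblings only.

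The cost is one more variable in the data file, somewhat wider intervals and an ICC that will be imprecise: 45 children at three to six per worker would mean only about 8 to 15 workers (45/6 to 45/3), and the true number is not given. Where siblings share a worker, the two effects will be hard to separate. In a simulated check, a test clustered on key worker with small-sample degrees of freedom brought the level back to about 5% and cost only 1 to 3 percentage points of power when the ICC was zero.

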### Economic evaluation

This analysis will quantify the benefits and costs of EYEP to society. Estimates of the net impacts of EYEP on children’s human capital development and service usage, and on outcomes for parents, will be translated into estimated monetary values, and these benefits aggregated to compare against the costs of the program, to arrive at a benefit-cost ratio for the program. The main potential benefits of the intervention are expected to derive from its effects on child health, cognitive development and interpersonal skills. Improved outcomes in these areas may yield benefits from: reduced direct cost to government such as reduced demands for health services, and reduced demand for specialized education due to better cognitive development. To assign monetary values to these benefits, we will for example collect information on the cost of health and special education services to estimate the values of reduced usage of those services. This information will then be combined with the estimated impacts of EYEP on service usage. The main costs associated with EYEP are the costs of providing the childcare and early education services; including employees’ wage costs, the cost of purchasing resources such as toys and educational materials, and maintenance costs for the program site. In undertaking the benefit-cost analysis of EYEP, it will be important to recognize what factors it may not be possible to value in monetary terms.

### Sample size and power calculations

The sample size has been determined taking into account both the numbers of observations needed to have sufficient power to detect likely effect sizes and the capacity of the CPS childcare centre where EYEP is being implemented. There is no previous Australian study of an intervention similar to EYEP, therefore calculation of the required sample size has been done using impact sizes estimated for the Abecedarian project. Impact sizes from the Abecedarian project are above those for most other early years programs
[21], however, this can be attributed to its being an extensive and long-term intervention. The similar scale of intervention in EYEP makes Abecedarian an appropriate benchmark for this study. We use impact estimates from the Abecedarian project for IQ at 18 months and at 48 months (
[35] page 1918).

The sampsi routine in STATA was used to calculate the necessary sample size. When type one error is set at 0.05 and type two error set at 0.1 (power = 0.9), the minimum required sample size (per group) is 12 children based on the impact on IQ at 18 months IQ and 19 children based on the impact on IQ at 48 months. We then adjust this required sample size in two ways. First, we take into account that our sample will include families with multiple children. Based on the sample from the pilot phase of EYEP we estimate the number of children per family to be 1.35. We assume perfect correlation of outcomes between siblings which therefore requires expanding the minimum sample size by 1.35. Second, we incorporate an estimated attrition rate of 20 per cent per annum for the intervention and control groups (including item non-response). These adjustments result in a minimum sample size per group of 32 children. Hence it is expected that the sample size of 45 children in intervention and control groups will comfortably meet sample size requirements. It also provides a margin of safety in case standard errors in estimates of the impact of EYEP are larger than for the Abecedarian trial. All children in the Abecedarian trial were enrolled prior to reaching 6 months of age, while children recruited into the EYEP trial have been from a broader range of ages, up to 3 years. To the extent that age of enrolment is a source of variability in impact sizes, our estimates of impact size may therefore have larger standard errors than the Abecedarian study.

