### Approaches to dealing with the problem

A variety of early years education and care programs targeted at increasing the human capital of disadvantaged children have been implemented. These programs have consisted primarily of intensive early years education and care and/or home visiting and parent education
[20], pp41-51].

Notable examples are the Perry Preschool program and the Abecedarian Project
[21], pp.115-16]. The Perry program provided one to two years of part-day education and weekly home visits for low-IQ African American children aged three to four years living in low-income households in Ypsilanti, Michigan, during the 1960s. The Abecedarian program provided year-round full-time center-based care for five years, starting from the first year of life, for mostly African American children from low-income households from Chapel Hill, North Carolina.

Programs that increase the human capital of children from disadvantaged backgrounds can benefit those individuals, and reduce inequality in childhood human capital development. Summary evidence on the impact of early years interventions is available from a meta-analysis of 84 studies of outcomes from programs implemented between the early 1960s and mid 2000s. Only studies that met minimum standards for quality of research methods were included in the review. The meta-analysis found an average effect size on cognitive and achievement scores of 0.35 standard deviations at the end of the treatment period. This effect decayed at a rate of 0.03 standard deviations per year after the end of treatment. Less evidence is at present available to evaluate the effect of early years programs on non-cognitive or behavioural outcomes; and findings are mixed
[21]. Other reviews of studies of early years programs obtain similar findings, with somewhat stronger evidence for effects on behavioural outcomes
[20, 22–26].

Early years interventions can also provide spillover benefits for society. By increasing the human capital of children from disadvantaged backgrounds, future expenditures that a society might otherwise be required to make are avoided

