### Intervention and control group

The intervention group participate for three years (or until school entry) in EYEP. The control group receive what we refer to as ‘usual care’. This is a mix of parental and guardian care, and education and care provided by other local childcare centres or kindergartens. The usual care is determined by the choice of the child’s parent(s) without any direction; that is, there is no direct effect on the control group’s early education and care due to participation in the EYEP trial.

Nevertheless, it is possible that the control group may be affected by participation in the trial. For example, awareness of EYEP and its objectives may alter the decisions that parents of children in the control group make about their children’s early education. In addition, all children receive an annual development report which may change decisions that control group families make about their children’s needs and which services to access. Hence we plan to construct an extra quasi-experimental control group by matching trial participants with a group of children with similar background characteristics from the Longitudinal Survey of Australian Children (LSAC). By collecting some data items on outcomes for trial participants that are also collected for children in LSAC, we will be able to compare outcomes for the EYEP intervention and control groups with a control group from general population survey of children.

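### The 90% power rests on Abecedarian effects of about 1.05 to 1.3 SD, justified by a similarity of scale that the article's own description of the two programmes does not bear out, with no allowance for a smaller mean effect

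*Protocol article*

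**What the plan says.** The article's Sample size and power calculations section names its source of effects: "We use impact estimates from the Abecedarian project for IQ at 18 months and at 48 months". It accepts that Abecedarian impacts exceed those of most early years programmes, attributes this to how extensive and long that programme was, and concludes: "The similar scale of intervention in EYEP makes Abecedarian an appropriate benchmark for this study".

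The error rates are given as "When type one error is set at 0.05 and type two error set at 0.1 (power = 0.9"). The required number per group is 12 from the 18-month effect and 19 from the 48-month effect. A sibling factor of 1.35 and attrition of 20% per annum bring the minimum to 32. The planned 45 is then said to meet the requirement comfortably, with a margin in case standard errors exceed Abecedarian's.

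On the programmes themselves:
- Abecedarian (Approaches to dealing with the problem): "year-round full-time center-based care for five years, starting from the first year of life". On entry age (Sample size section): "All children in the Abecedarian trial were enrolled prior to reaching 6 months of age".
- EYEP (Intervention and control group): "The intervention group participate for three years (or until school entry) in EYEP". The Participants section admits children aged 0 to 3 years.

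The Sample size section discloses the wider range of entry ages, but draws from it only that standard errors may be larger.

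The Background also cites a meta-analysis of 84 studies with an "average effect size on cognitive and achievement scores of 0.35 standard deviations at the end of the treatment period".

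**The concern.** The article explains Abecedarian's unusually large effects by the length and extent of that programme, then borrows them on the ground that EYEP is alike in scale. Length and age at entry are features on which the article's own description shows EYEP to differ. If long, early exposure explains a large effect, then later entry and shorter exposure may mean a smaller one. The article allows for more noise but not for a smaller mean.

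Neither the IQ differences nor their standard deviations are printed, so a reader cannot see how large an effect the trial was sized to find. At stake is how a non-significant result would be interpreted. If the trial has good power only for effects near 1 SD, such a result says little about moderate effects, yet the current wording suggests that the sample is ample.

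**Working it through.** **Inputs.** From the Sample size section: alpha 0.05, power 0.90, n = 12 and 19 per group, sibling factor 1.35, attrition 20% per annum, adjusted minimum 32, planned 45 per group. From the Background: 0.35 SD. Evaluations at 12, 24 and 36 months after entry come from the Design and Data analysis sections. Assumptions: a two-sided test (sidedness is not stated) and equal allocation. The 0.5 SD below is an illustrative value.

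**Step 1: the plan's own figure.** The minimum of 32 can be reached in two ways:
- 48-month effect with one year of attrition: 19 × 1.35 / 0.8 = 32.1.
- 18-month effect with three years of attrition: 12 × 1.35 / 0.8³ = 16.2 / 0.512 = 31.6.

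The article does not say which applies. The 12 and 19 cannot be checked independently, because no IQ difference or SD is printed.

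**Step 2: the implied effects.** For two means, d = (1.960 + 1.282) × √(2/n).
- n = 12: 3.2415 × √(2/12) = 1.32 SD.
- n = 19: 3.2415 × √(2/19) = 1.05 SD.

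A one-sided test would imply 1.19 and 0.95 SD. The two-sided values are 1.32/0.35 = 3.8 and 1.05/0.35 = 3.0 times the average that the article cites.

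**Step 3: the effective number at each evaluation.** This is 45 / 1.35 × 0.8^t, with t in years:
- 12 months: 33.33 × 0.8 = 26.7
- 24 months: 33.33 × 0.64 = 21.3
- 36 months: 33.33 × 0.512 = 17.1

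**Step 4: what 45 per group detects.** Detectable effects use the formula in Step 2; power uses the noncentral t distribution.

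| Evaluation | Effective n per group | Effect with 90% power | Power at 0.35 SD | Power at 0.5 SD |
|---|---|---|---|---|
| No adjustment | 45 | 0.68 SD | 38% | 65% |
| 12 months | 26.7 | 0.89 SD | 24% | 43% |
| 24 months | 21.3 | 0.99 SD | 20% | 36% |
| 36 months | 17.1 | 1.11 SD | 17% | 29% |

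With the noncentral t, the detectable effects become 0.69, 0.90, 1.02 and 1.14 SD.

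**Step 5: the size of the margin.** Against the 48-month benchmark of 1.05 SD, 45 per group keeps 90% power down to 0.89/1.05 = 85% of the benchmark at 12 months and 0.99/1.05 = 94% at 24 months. At 36 months there is no margin: 1.11 exceeds 1.05, and the required number is 19 × 1.35 / 0.512 = 50.1, above 45. Against the 18-month benchmark of 1.32 SD, a margin remains at all three evaluations (1.11/1.32 = 84% at 36 months).

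**The case against.** Much can be said for the plan. It discloses the difference in entry age, says that Abecedarian's effects are above most, and states that centre capacity also limited the sample. The 0.35 SD figure averages many varied programmes, so preferring a benchmark closer to an intensive one is a defensible judgement. Programmes may also be alike in scale without having the same length. All of this stands. It makes the choice of benchmark arguable, but it does not supply the missing allowance for a smaller mean effect.

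Some stronger readings are tempting, and the documents do not support them:
- A reader might compare months of programme received by ages 18 and 48 months and conclude that EYEP children would have had very little. EYEP evaluations are timed from entry, so exposure can reach 12, 24 and 36 months whatever the entry age, apart from school entry. Nor had the full five years of Abecedarian been delivered at the ages borrowed. Up to 12 months of EYEP is close to the exposure behind the 18-month benchmark; 36 months falls short of that behind the 48-month one.
- A reader might infer that eligibility excludes the benchmark population. It does not: children are eligible from age 0, so infants under 6 months form a subset.
- A reader might infer that the margin cannot cover a smaller effect. Power depends on the ratio of effect to standard error, so spare sample absorbs some of either; Step 5 of the working shows how much.
- A reader might infer that power falls by a known amount. No passage gives an effect by entry age or exposure. The plan's own figures even imply a larger effect at 18 months than at 48.

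Analysing change from baseline could raise power if the baseline correlation exceeds 0.5, but the sample size section claims no such gain.

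**Conclusion.** The point holds as a fault in justification. The arithmetic to 32 can be reproduced, but the effects behind it, about 1.05 and 1.3 SD, are carried over on a similarity that the article's own figures on duration and entry age do not bear out. Later entry is treated as a matter of variance alone. The stated 90% power is therefore not supported for the population EYEP admits; that is different from being shown wrong by a stated amount.

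With the plan's own factors, the trial has 90% power only for effects of roughly 0.9 to 1.1 SD across the three annual evaluations. The claim of comfort also fails at 36 months on the 48-month benchmark. These figures assume a two-sided 5% test, the plan's perfect sibling correlation, attrition compounding at 20% each year, and no gain from baseline adjustment.

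**What to change.** In the Sample size and power calculations section:
1. Remove the sentence resting on similarity of scale and the word *comfortably*.
2. Print the IQ differences and SDs used, with the standardised effects behind 12 and 19 (about 1.3 and 1.05 SD), and state that the test is two-sided if it is.
3. State what 45 per group detects with 90% power after the 1.35 factor and 20% per annum attrition: about 0.9 SD at 12 months, 1.0 SD at 24 and 1.1 SD at 36, against about 0.7 SD with no adjustment.
4. Show power at smaller effects for the same evaluations: about 24%, 20% and 17% at 0.35 SD, and about 43%, 36% and 29% at 0.5 SD.
5. Say that later entry and shorter exposure may lower the mean effect as well as widen its standard error, and that a non-significant result will be read from its confidence interval.

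The cost is wording and a short table. No extra children are needed, but the power statement becomes less favourable.

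### The 1.35 sibling inflation fits an analysis that counts each family once; for the child-level means the plan compares, its own assumptions give at least 1.52 at entry, so the stated minimum of 32 per group is a few children too low

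*Protocol article*

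**What the plan says.** The section on sample size and power in the protocol article starts from a requirement at 5% type I error and 90% power: "the minimum required sample size (per group) is 12 children based on the impact on IQ at 18 months IQ and 19 children" for IQ at 48 months. It then makes two adjustments.

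- Siblings: from the pilot, "we estimate the number of children per family to be 1.35". The step that follows is: "We assume perfect correlation of outcomes between siblings which therefore requires expanding the minimum sample size by 1.35".
- Attrition: a yearly loss of 20% in both groups, which includes item non-response.

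The result is a "minimum sample size per group of 32 children", which the section sets against 45 planned per group and describes as comfortably covered.

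Two other sections fix how siblings enter. Under Randomisation, all participating children of a family go to one arm, and siblings born later follow the older child. Under Data analysis, the intention-to-treat effect is estimated "at the level of the individual child", as a difference in mean change between groups, with t-tests for single outcomes. No averaging within families and no family weights are described.

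**The concern.** The sample size section presents 1.35 as the consequence of perfect sibling correlation. It is that consequence only when each family counts once, or when all families are the same size. Whole-number family sizes cannot all equal 1.35. In a mean over children, a two-child family carries twice the weight of a one-child family while adding no more information, so precision falls further than the mean family size suggests.

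At stake are the stated minimum of 32, the nominal 90% power attached to it, and the size of the margin claimed for 45 per group. The text also leaves a reader unsure whether families or children are meant to be weighted equally.

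**Working it through.** **Inputs, all from the protocol article.** Base requirement 19 per group (IQ at 48 months); mean 1.35 children per family; sibling correlation 1; attrition 20%; stated minimum 32; planned 45 per group; power 0.90; type I error 0.05, taken here as two-sided because the article does not say. The distribution of family sizes is not given.

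**Step 1: the plan's own figure.** 19 × 1.35 = 25.65, and 25.65/0.8 = 32.06, which rounds to the stated 32 (33 if rounded up). This uses one 20% loss. Another route, 12 × 1.35/0.8³ = 31.64, also rounds to 32.

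**Step 2: the factor.** Let m be the number of trial children in a family, all sharing one value with variance σ².

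- Mean over children: variance σ²·Σm²/(Σm)². Relative to σ²/Σm for independent children, the inflation is Σm²/Σm = E[m²]/E[m].
- One value per family: the inflation is E[m] = 1.35.

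**Step 3: a lower bound without knowing the mix.** For whole numbers m ≥ 1, (m − 1)(m − 2) ≥ 0, so m² ≥ 3m − 2. Hence E[m²] ≥ 3 × 1.35 − 2 = 2.05, and the factor is at least 2.05/1.35 = 1.5185. Equality holds with 65% one-child and 35% two-child families. If all families with siblings had three children (82.5% and 17.5%), the factor would be (0.825 + 9 × 0.175)/1.35 = 1.78. A simulation with the 65/35 mix gave 1.52 for the child-level mean and 1.35 for one value per family.

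**Step 4: restated minimum, single attrition step.**

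- Whole families lost: 19 × 1.5185/0.8 = 36.06, so 36 to 37 depending on rounding. By the other route, 12 × 1.5185/0.8³ = 35.6.
- Siblings lost independently, 65/35 mix, retention p = 0.8: the factor among retained children is (1 − p) + p × 1.5185 = 1 + 0.8 × 0.5185 = 1.415. Then 19 × 1.415/0.8 = 33.6, so about 34.

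**Step 5: power, normal approximation throughout.** The benchmark effect and SD are not given, but 19 per group at 90% power implies a standardised difference d = √(2/19) × (1.960 + 1.282) = 1.05. With effective size n per group, power = Φ(d√(n/2) − 1.960). For whole-family dropout:

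| Enrolled per group | Effective n, factor 1.35 | Power | Effective n, factor 1.5185 | Power |
|---|---|---|---|---|
| 32 | 25.6/1.35 = 18.96 | 0.90 | 25.6/1.5185 = 16.86 | 0.86 |
| 45 | 36/1.35 = 26.67 | 0.97 | 36/1.5185 = 23.71 | 0.95 |

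**The case against.** Several points on the other side stand.

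- **The planned size survives this defect.** With one attrition step, 45 exceeds 37. A reader might infer that the correct factor makes the trial too small, because 20% a year compounded over three years gives 19 × 1.5185/0.512 = 56.4. But under that compounding the plan's own 1.35 already gives 19 × 1.35/0.512 = 50.1, also above 45. What takes the requirement past enrolment is the handling of yearly attrition, which is a separate issue.
- **The 1.52 floor applies at entry.** Because the attrition figure includes item non-response, one sibling may be missing and the other not, which lowers the factor in the analysed sample. The article does not say which pattern is expected, so 34 to 37 is the fair range for one- and two-child families.
- **Perfect correlation is a worst case.** With the 65/35 mix at entry, the factor at sibling correlation ρ is 1 + 0.5185ρ, which equals 1.35 at ρ = 0.35/0.5185 = 0.675. A reader might infer that the trial will be less precise than reported. The documents do not show that, because the true correlation is unknown and 1.35 is adequate up to about 0.675.
- **The analysis is described briefly.** A model with a family effect would, at correlation near 1, weight families about equally and support 1.35. Such detail may sit in an analysis plan that is not shown.

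The last point does not remove the inconsistency. The article asserts a specific factor as the one its assumption requires, and describes an unweighted comparison of children to which that factor does not apply. Nor is the missing family-size distribution an escape, since 1.52 is the minimum over every whole-number mix with mean 1.35.

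**Conclusion.** The point holds as an inconsistency of modest size. Under the plan's stated assumptions of perfect sibling correlation and 1.35 children per family, 1.35 does not match an equally weighted child-level comparison; the matching factor is at least 1.52 at entry. With the single 20% loss that reproduces 32, the minimum should read at least 36 to 37 per group if families leave whole, or about 34 for one- and two-child families if siblings are lost independently.

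In the whole-family case, the power at 32 per group is about 0.86 and the margin of 45 over the minimum shrinks from 13 children to 8. Power at 45 is still about 0.95. On this ground alone, neither an inadequate sample size nor lower actual precision is shown. The power figures rest on two-sided testing, the normal approximation and the standardised difference implied by 19 per group.

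**What to change.** Make the inflation factor and the analysis agree, in one of two ways:

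1. Keep 1.35 and state that each family has equal weight, by analysing the sibling mean or by weighting each child by one over the number of siblings in the trial.
2. Keep the equally weighted child-level mean, replace 1.35 by at least 1.52, state the assumed family-size mix and whether siblings are expected to drop out together, and restate the minimum sample size and the power at 45 per group.

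If a sibling correlation below 1 is thought realistic, say so and derive the factor from it.

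The first option costs a sentence on weighting and shifts the target from the average child to the average family. The second costs a few lines and a somewhat less favourable stated margin. Neither requires a change in enrolment.
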